### Sample size

As our primary outcomes are feasibility it is desirable to keep the sample size small enough to allow close monitoring of participants and the programme while large enough to obtain sufficient data on our primary outcomes of feasibility. For feasibility reasons we will ensure we have sufficient numbers in each group to generate a ‘group’ climate likely to maximise adherence. Hence if the group gets too small, it becomes unviable for participant engagement and sense of community. The minimum numbers required to sustain a community-based music and movement programme and maintain the required group dynamics is between 10–12 older adults per group; guided by practice expertise within the research team and previous feasibility studies (
Clifford *et al.*, 2021;
O’Regan *et al.*, 2020). The primary feasibility outcomes will be evaluated by assessing recruitment rates (the rate of participants recruited to the study); retention rate (the number of participants who complete measures at baseline and at follow up post intervention) and minimum average attendance (number of participants who attended at least 65% of the intervention sessions). Hence, we aim to recruit a minimum of 72 participants in total (n=12 per cluster) allowing for 20% attrition (n=60; n=10 per cluster), we will be able to estimate a recruitment rate of 60% within a 95% confidence interval +/- 12.6%; a retention rate of 80% within a 95% confidence interval of +/- 10.3% and a minimum average attendance of 65% within a 95% confidence interval of +/- 12.3%. 

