### Randomisation

Pragmatic randomised controlled trials (RCTs) are conducted to answer the important question of how an intervention works in real-world contexts in a heterogeneous real-world population. Thus, we plan to recruit individuals in the Mid-West of Ireland from at least six geographical regions or clusters; the groups of study participants are the units of randomisation (clusters), and individuals within these groups are the units of analysis. The clusters are based on the geographical regions where the participants reside (two clusters in each county n=6 geographical regions, with n=2 additional reserve clusters sites). Using block randomisation, the clusters will be randomised to either the intervention or control (usual care) using 1:1 allocation ratio. Thus, there will be an intervention and a control group in each county. Given the wide geographical spread of these locations, it would be impractical to conduct an RCT by randomising participants individually to either the intervention or control arm and then find a central location to conduct the intervention. Additionally, this approach would not keep the community groups together. The cluster RCT design will ensure we keep community groups together. Research from a recent cluster-randomised controlled study, demonstrated that being ‘
*part of a local community group*’ can afford additional benefits, including an increased likelihood to remain active due to the friendships they had formed (OR=3.04, 95% CI=1.65–5.60, p=0.001), as a result of attending of the programme (
O'Regan *et al.*, 2021). In line with our pragmatic approach the study will have two phases for recruitment and two implementation blocks as the intervention can apply naturally to the group. Participants in the same group will receive the same intervention, thus approximating clinical practice, and producing generalisable findings.

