	To explore the differences between the groups for Physical Function, Balance, Physical Activity, Loneliness, Social Isolation, Mood, and Quality of Life.	Results for each outcome of interest.	We can determine the required sample size for a definitive trial.	ICC (intraclass correlation coefficient) will be used to calculate the design effect. Thus, the required sample size for a CRCT (cluster-randomised controlled trail) will be calculated by multiplying the required sample size for the equivalent ungrouped study with the DE.
	Pilot economic analysis to assess costs and inform a definitive trial.	A pilot economic analysis to inform the design and conduct of a full economic evaluation to assess the cost effectiveness of the programme developed.	The methods developed and implemented for the conduct of the pilot health economic analysis proved to be feasible and acceptable to study participants.	The criterion for success includes obtaining sufficient data on cost. Incremental analysis to calculate the mean differential in costs and QALYs. The incremental cost effectiveness ratio (ICER) will be calculated and analysed. Parametric and probabilistic analyses will be employed to explore uncertainty.

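### Table 1 says the pilot can determine the definitive trial's sample size through an ICC, but six clusters cannot estimate an ICC well enough to do that

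*Protocol article*

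**What the plan says.** The secondary part of Table 1 (printed under Process evaluation) has a row on sizing the next trial. Its hypothesis cell reads "We can determine the required sample size for a definitive trial". The analysis cell gives the route: "ICC (intraclass correlation coefficient) will be used to calculate the design effect". The sample size of an individually randomised trial is then multiplied by that design effect. The outcome cell refers to the results for each outcome, so the natural reading is that the ICC comes from this pilot. The row names no external ICC, range or confidence limit to carry forward.

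The Randomisation section sets the number of clusters: "two clusters in each county n=6 geographical regions, with n=2 additional reserve clusters sites". Allocation is 1:1, which gives three clusters per arm. The Sample size section sets the cluster size: "we aim to recruit a minimum of 72 participants in total (n=12 per cluster) allowing for 20% attrition (n=60; n=10 per cluster"). That section justifies the total by the precision of three proportions (recruitment, retention and attendance). It gives no precision for an ICC.

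**The concern.** An ICC rests on how much cluster means differ, so its precision depends mainly on the number of clusters and much less on the number of people. Three clusters per arm leave 4 degrees of freedom between clusters. An estimate on that basis is often zero or negative, which would imply no inflation for clustering, and otherwise it is widely scattered.

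The study exists to prepare a definitive trial, and this row is where its data become that trial's size. If the row is followed as written, chance in six clusters could leave the next trial underpowered or needlessly large.

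**Working it through.** **The plan's own precision figures.** The article gives no figure for the ICC. Its only precision figures are half-widths of 12.6, 10.3 and 12.3 percentage points for proportions of 60%, 80% and 65%. They reproduce from 1.96 × √(p(1−p)/n) with n = 58 (72 × 0.8 = 57.6): 12.61, 10.29 and 12.28. They describe proportions and say nothing about an ICC.

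**Inputs from the article.** k = 6 clusters, 3 per arm; m = 10 analysed per cluster.

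**Assumptions.** True ICC ρ = 0.01, 0.05 or 0.10; equal cluster sizes; a normally distributed outcome; arm removed before the ICC is estimated; the next trial also has 10 analysed per cluster.

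**Method.** This is the one-way ANOVA estimator with its exact F distribution.
- Degrees of freedom: 6 − 2 = 4 between clusters and 6 × 9 = 54 within.
- The ratio of mean squares divided by θ follows F(4, 54), where θ = 1 + mρ/(1 − ρ).
- ICC estimate = (F − 1)/(F + m − 1). Design effect = 1 + (m − 1) × ICC.
- The 2.5th and 97.5th percentiles of F(4, 54) are 0.1194 and 3.034.

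**Worked case, ρ = 0.05.**
- θ = 1 + 0.5/0.95 = 1.526.
- Chance of an estimate at or below zero: P(F(4, 54) ≤ 1/1.526) = 0.37.
- 97.5th percentile: F = 1.526 × 3.034 = 4.63; ICC = 3.63/13.63 = 0.266; design effect = 1 + 9 × 0.266 = 3.40.
- True design effect = 1 + 9 × 0.05 = 1.45. Oversizing = 3.40/1.45 = 2.3 times.
- If the estimate is zero, the design effect is taken as 1. The trial is then 1 − 1/1.45 = 31% too small. Power planned at 80% becomes Φ(2.80/√1.45 − 1.96) = 64%.

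**All three assumed values, 10 per cluster.**

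| True ICC | Estimate ≤ 0 | True design effect | 97.5th-percentile design effect | Oversizing there | Shortfall if estimate is zero | Power then |
|---|---|---|---|---|---|---|
| 0.01 | 53% | 1.09 | 2.7 | 2.5 times | 8% | 77% |
| 0.05 | 37% | 1.45 | 3.4 | 2.3 times | 31% | 64% |
| 0.10 | 25% | 1.90 | 4.2 | 2.2 times | 47% | 53% |

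**Confidence interval around an observed ICC of 0.05.** The observed F is 1.526.
- Lower limit: 1.526/3.034 = 0.503, so ICC = −0.497/9.503 = −0.05.
- Upper limit: 1.526/0.1194 = 12.78, so ICC = 11.78/21.78 = 0.54.

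**Sensitivity at ICC 0.05.**
- Both reserve clusters used (8 clusters, 6 and 72 df): estimate at or below zero in 31%; 95% CI −0.04 to 0.40.
- Twelve analysed per cluster: 95% CI −0.04 to 0.51; 97.5th-percentile design effect 3.68 against a true 1.55, or 2.4 times.
- County removed as well as arm, since each county has one cluster per arm (2 df): estimate at or below zero in 48%; upper limit 0.86.

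**The case against.** Several points on the other side are fair.

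- **Inferred content.** The row does not say outright that the ICC is the pilot's own, nor that a bare point estimate will be used. The Data analysis section emphasises description and confidence intervals in general. A reader might infer that the point estimate is to be treated as known; the text does not say so. The pilot origin, by contrast, follows reasonably from the outcome cell.
- **The ICC model.** A reader might infer that arm will be left out, so that a treatment effect would inflate the ICC. The article specifies no ICC model, and that detail commonly belongs in the analysis plan. It is no part of this point.
- **Size of the error.** It is tempting to say that the next trial would be mis-sized several-fold. That describes the width of the confidence range for the design effect (about 1.0 to 5.9 for an observed ICC of 0.05). It does not describe the error from using the estimate itself, which is about 2.2 to 2.5 times too large at the 97.5th percentile, or 8% to 47% too small when the estimate is zero. At an ICC of 0.01 the loss of power is minor.
- **Prominence.** Sizing stands in the hypothesis column of one secondary row and is not listed among the study's aims. It affects no result of the present trial.
- **Standard practice.** Multiplying by a design effect is standard, reporting a pilot ICC is normal, and six clusters is a minimum.

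These points limit the reach of the concern but do not remove it. The row states a capability that six clusters do not give, and eight do not give it either. An analysis plan that added external ICCs would still leave this published statement in need of correction.

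**Conclusion.** The point holds as a correction to a stated claim. On the natural reading that the pilot's own ICC is meant, six clusters cannot determine the definitive sample size by this route. The size of the error depends on the true ICC, which the article does not give, so the figures should be read as a range over 0.01 to 0.10. Across that range, between a quarter and a half of pilots would suggest no clustering at all. The conclusion is stable to 10 or 12 per cluster and to use of the reserve clusters. The present trial's feasibility results are unaffected. It should be changed because it bears directly on the planning of the next trial.

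**What to change.** In the Table 1 row:

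1. Reword the hypothesis so that the pilot will *inform*, rather than determine, the definitive sample size.
2. Report the pilot ICC for each outcome with its 95% CI, as descriptive only.
3. Calculate the definitive sample size over a stated range of ICCs from comparable external cluster trials (for example 0.01 to 0.10). Use this pilot for the outcome SD, retention and variation in cluster size.

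The cost is a more modest claim and a literature search when the next trial is planned. The present trial needs no new data and no change of design.

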### Data analysis

The quantitative data collected for this research will be input into IBM SPSS Statistics software package (version 27). As this is a feasibility study, the analysis will focus on descriptive statistics and confidence interval estimation. Continuous variables will be reported as means, standard deviation and 95% confidence intervals, and categorical data as the number and percentages. A content analysis will be performed on any data from open-ended questions. Qualitative data collected for this research will be analysed according to Braun and Clarke's 6-step framework for doing inductive thematic analysis, including familiarisation and theme generation, searching, reviewing and defining (
Braun & Clarke, 2019). Investigator triangulation will support integrity in the data analysis process. Thus, sample transcripts will be independently coded by members of the research team to discuss and agree on the codes and interpretations. The research team will meet to discuss the dataset and develop consensus around coding, interpretations, patterns, ideas and themes. NVivo software (London, United Kingdom) will be used to code and analyse the data using built-in functionality. The themes will be reviewed and discussed by all members of the research team to generate a thematic 'map' of the analysis.

### Trial Governance and data management

This trial will be conducted in accordance with international standards of good practice in clinical trials (ICH GCP Good Clinical Practice). A Trial Management Committee (TMC), a Trial Steering Committee (TSC) and Independent Data Monitoring Committee (IDMC) will be convened to ensure adequate trial management, governance and safety monitoring for the trial. The Health Research Institute (HRI) Clinical Research Support Unit Limerick (CRSU Limerick) will provide support with document development, data quality, data storage, and archiving of data in line with good clinical practice (GCP) standards as well as FAIR (findable, accessible, interoperable, and reusable) principles for scientific data management and stewardship. An electronic database (CRFWEB) has been developed to facilitate data collection and management. CRFWEB is a secure cloud-based electronic data capture software which enables the researchers to collect, integrate, and manage data. CRFWEB will run regular data validation checks, provide a range of data audit and data trails, automatically raised queries and offer multiple layers of security. The independent data monitoring committee (IDMC), which includes an independent trial statistician, the CRSU manager, and an independent clinician, will monitor data emerging from the trial, in particular in relation to safety and efficacy, and make any recommendations as required to the Trial Steering Committee (TSC).

### Ethics approval

Ethics approval for this study has been granted by the Faculty of Education and Health Sciences Research Ethics Committee at the University of Limerick (EHSREC No: 2022_01_08_EHS). During the recruitment phase, potential participants will be provided with information about the study, where they will have the opportunity to read about the study and ask any questions about the study prior to providing written informed consent to participate. The information sheet will contain all relevant information, including the aim, nature of the study, procedures, confidentiality, possible risks, benefits, and freedom to withdraw without consequence in advance of deciding to participate. The research team will preserve the confidentiality of participants taking part in the study in line with GDPR guidelines.

### Plans for dissemination of the study outcome

Dissemination of the research findings will follow the World Health Organisation Research Dissemination recommendations (
WHO, 2014) and a Patient and Public Involvement (PPI) Ignite developed PPI Dissemination Planning tool. As a priority, we aim to disseminate the findings of the study to local, national and international audiences via relevant meetings, conferences and peer-reviewed academic journals. All outputs will be prepared using language that is appropriate for the target audience.

### Study status

The study is currently ongoing. The expected end date for the study is April 2023.

## Discussion

This protocol outlines the design of the study titled ‘
*Music and Movement for Health: Protocol for a pragmatic cluster-randomised feasibility pilot trial of an arts-based programme for the health and wellbeing of older adults*’. The aim of the
*Music and Movement for Health* project is to assess the feasibility of a comprehensively designed complex arts-based programme that has the potential to target several important interrelated psychosocial and physical factors in older adults. The programme will be developed through a systematic multi-stage process to optimise effect, buy-in and participation. The overall aim is to evaluate the feasibility of a future definitive pragmatic, cluster-randomised, controlled trial to evaluate the effects of a tailored community-based arts-based health programme for older adults in a community setting in Ireland. The study also aims to examine if, how, and why the arts-based programme was successful at producing the desired outcomes. To the best of our knowledge, such a study has not been previously conducted in the Irish context. Given that a significant number of older adults are not meeting the recommended physical activity guidelines as well as the impact of the COVID-19 pandemic on levels of social isolation, loneliness and physical deconditioning, the assessment of a community-based arts programme is a priority for research as well as the provision of services. This study would be a significant step in gauging the feasibility and helpfulness of a community arts-based health programme and would be of benefit to clinicians, service-planners and policymakers working in the field of older adult healthcare.

## Data Availability

No data is associated with this article. Open Science Framework: Music and Movement for Health: Protocol for a pragmatic cluster-randomised feasibility pilot trial of an arts-based programme for the health and wellbeing of older adults.
https://doi.org/10.17605/OSF.IO/5NYRM (
Clifford, 2022). This project contains the following extended data: Appendix 1: WHO registration data set Appendix 2: CONSORT 2010 Flow Diagram Movement and Music for Health Appendix 3: Participant Consent Form Appendix 7: Falls Calendar Open Science Framework: SPIRIT checklist for ‘
*Music and Movement for Health*: Protocol for a pragmatic cluster-randomised feasibility pilot trial of an arts-based programme for the health and wellbeing of older adults’.
https://doi.org/10.17605/OSF.IO/5NYRM (
Clifford, 2022). Appendix 4: SPIRIT 2013 Checklist: Recommended items to address in a clinical trial protocol and related documents Appendix 5: CONSORT 2010 checklist of information to include when reporting a cluster randomised trial Appendix 6: CONSORT 2010 checklist of information to include when reporting a pilot or feasibility trial Data are available under the terms of the
Creative Commons Zero "No rights reserved" data waiver (CC0 1.0 Public domain dedication).
